## Study design - overview

The FLEX Study is a cluster randomized controlled trial. Participating schools were clustered by location within the state and school district. Schools within each district were randomly assigned to receive a school-based PA intervention (*100 Mile Club* or *Just Move*) or assigned to be a control school. Third and fourth grade students were enrolled and are being followed for two school years (Fig. 1). Data are collected at three time points: baseline (fall, school year 1), short-term (spring, school year 1; 5–6 months post-baseline) and long-term post-intervention (spring, school year 2; ≈1.5 years post-baseline). The study occurred in two waves, the first beginning during the 2014–2015 school year (*n* = 6 schools) and the second wave during the 2015–2016 (*n* = 18 schools) school-year. Due to unforeseen weather circumstances and school cancellations in Winter 2015, additional student participant recruitment beyond the initial six schools was put on hold until the following school year. The investigative team determined that these schools would be designated as Wave 1. Approval for the study was obtained from the Tufts University IRB (Medford, MA) and additionally from individual school districts where required.

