## Setting & participants

### Schools

Identification of eligible schools began at the district level. The FLEX study is designed to examine health disparities among children associated with income and race/ethnicity. Therefore we targeted lower income and racially/ethnically diverse public school districts in Massachusetts. Initially, school districts were approached for participation if they had greater than 40 % of students qualifying for free or reduced price lunch and/or had greater than 40 % non-Caucasian students. In addition, districts were only approached if they had at least four elementary schools serving 3rd-5th graders.

Overall, twenty school districts were approached. Twelve of these districts declined to participate, citing changes in administration, ongoing participation in similar programs, and/or competing priorities. From the remaining eight districts, 24 schools agreed to participate and have at least one school enrolled. Six schools were included in Wave 1 and 18 schools in Wave 2. All districts serve a low-income and diverse population and are located in urban, suburban, and peri-urban areas. One exception to the initial inclusion criteria was made, such that one school from a district with 34 % low-income students was included.

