## Sample size calculation and data analyses

A priori sample size calculations for the FLEX study were based on several recent school-based physical activity interventions. Power calculations for our analysis with respect to school-time MVPA were based on the findings of Verstraete et al. [51]. In this study, the intervention group showed a greater percentage of recess time spent in MVPA, compared to controls (mean ± SD: 53.4 ± 25.6 vs. 43.5 ± 27.6). While we expect a larger difference from our more intensive intervention, we used this conservative estimate to calculate our sample size, resulting in an estimated sample size of 115 participants per arm (total *n* = 345) with power of 80 %. For total daily MVPA, we referred to the findings from a RCT to increase PA through curriculum modification by Donnelly et. al [52]. In this study, the intervention group received 90-min/week of physically active classroom lessons (≈10 min/lesson) which resulted in an increase of 26 min of weekly MVPA in the intervention group compared to controls (within group SDs = 40). We estimated that a sample size of 39 per arm (117 total) is needed to detect differences of this magnitude. Thus, the sample size of 345 will be sufficient. Because the number of clusters is fixed at 21 schools, 7 per arm, we used a protocol suggested by Hemming et al. [53] to adjust for the clustering. Assuming an ICC of 0.03 and attrition rate of 25 % per year, we arrived at a final sample size of 903 students, 43 per school.

During the 2014–2015 study roll out, Boston experienced a severe snow season which impacted the school recruitment process. After consulting with the funding agency we subsequently extended school recruitment and intervention implementation into the next year, creating the two-wave structure described previously.

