For statistical analyses, descriptive statistics for variables of interest will be compiled and tabulated. To test the effect of school-based PA programs on minutes spent in MVPA, we will compare *100 Mile Club* vs. control and *Just Move* vs. control as separate tests using mixed effects models. Outcomes of interest are changes in minutes of MVPA between midpoint vs. baseline and post-intervention vs. baseline. The key regression coefficient of interest is the intervention by time interaction term, which will indicate if the intervention is associated with a significant higher/lower change in MVPA across time compared to the control. The unique school identification number will be modeled as random intercepts to adjust for clustering. We will examine both unadjusted and adjusted (including covariates such as sex, race/ethnicity, weight status) regression coefficients of the respective program and conclude if the difference in MVPA minutes is statistically significant. A similar approach will be used to examine the impact of PA programming on academic/cognitive outcomes. All analyses will be performed using SAS 9.3 (Cary, NC, USA) and results with p-values less than 0.05 will be considered statistically significant.

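### The school random intercept named as the clustering adjustment drops out of the intervention-by-time term that carries the test, so between-school variation in change is not in the stated model

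*Protocol article*

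**What the plan says.** Under Study design - overview: "The FLEX Study is a cluster randomized controlled trial". The same children are measured at baseline, midpoint and post-intervention: "Third and fourth grade students were enrolled and are being followed for two school years".

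Under Sample size calculation and data analyses, the targets are differences over time: "Outcomes of interest are changes in minutes of MVPA between midpoint vs. baseline and post-intervention vs. baseline". The test is then named: "The key regression coefficient of interest is the intervention by time interaction term". Clustering is handled by this sentence: "The unique school identification number will be modeled as random intercepts to adjust for clustering". The section names no school-by-time effect. It adds that academic and cognitive outcomes will be handled in a similar way.

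The same section sizes the trial for clustering. "Because the number of clusters is fixed at 21 schools, 7 per arm", it inflates the individual-level sample "to adjust for the clustering" at an ICC of 0.03. Under Schools, the number actually enrolled is higher: "From the remaining eight districts, 24 schools agreed to participate", or about 8 per arm.

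**The concern.** Schools were randomised, so a difference in change between arms has to be judged against how much change varies from school to school. A school intercept describes how schools differ in level. It is constant over visits and subtracts out when one visit is compared with another. The device the article names for clustering therefore cannot do that job for the coefficient the article names as the test.

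Schools in this trial could plausibly differ in their change. The article lets the walking/running program take place before, during or after school, leaves the classroom breaks to individual teachers, and reports baseline and follow-up measurement windows that differ between the waves.

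At stake is the error rate of the main MVPA comparisons and, since the approach carries over, of the cognitive and academic ones. The design pays for clustering in recruitment, but the stated test does not account for the part of it that affects the tested term.

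**Working it through.** **1. The plan's own sample size reproduces.** The individual-level calculation gives 115 per arm (difference 53.4 − 43.5 = 9.9, SDs 25.6 and 27.6, 80% power, two-sided 5%, noncentral t). With k = 7 schools per arm and ICC 0.03:

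m = n(1 − ICC)/(k − n·ICC) = 115 × 0.97/(7 − 3.45) = 31.4, rounded to 32 per school.

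Then 32/0.75 = 42.7, rounded to 43, and 43 × 21 = 903. The design effect at 32 per school is 1 + 31 × 0.03 = 1.93. The sizing therefore does allow for clustering.

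**2. The tested standard error does not respond to the school intercept.** Take 7 schools per arm, 32 children per school, balanced data, residual variance 1 and school-intercept variance τ².

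- Interaction (one follow-up against baseline): SE = √[4/(k·m)] = √(4/224) = 0.1336. It contains no τ².
- Arm difference at a single visit: SE = √[2(τ²/k + 1/(k·m))].

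| τ² | SE, arm difference at one visit | SE, arm × time |
|---|---|---|
| 0 | 0.094 | 0.1336 |
| 0.1 | 0.194 | 0.1336 |
| 1.0 | 0.543 | 0.1336 |

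With unbalanced attrition, the interaction SE moved only from 0.1278 to 0.1286 over the same range of τ², so the cancellation is then near-complete.

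**3. Size of the error for the model exactly as written.** Set total variance to 1, with school share vs = 0.03 (the article's ICC) and within-school share vc = 0.97. Let rs be the correlation of a school's effect between visits and rc that of a child's deviation. The documents give neither, so both are assumed: rs 0.3 to 0.8, rc 0.3 to 0.7. For children per school, enrolment is 174 + 1008 = 1182 in 24 schools, about 49 each. One year's 25% loss leaves about 37, two years' about 28.

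True variance ÷ model variance of the contrast = [vs(1 − rs)m + vc(1 − rc)] / [vc + vs(1 − rs)]

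- m = 37, rs = 0.3, rc = 0.3: (0.777 + 0.679)/0.991 = 1.47
- m = 37, rs = 0.8, rc = 0.7: (0.222 + 0.291)/0.976 = 0.53
- m = 28, rs = 0.8, rc = 0.7: (0.168 + 0.291)/0.976 = 0.47
- m = 37, rs = 0.55, rc = 0.5 (middle of the range): (0.4995 + 0.485)/0.9835 = 1.00

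The real type I error is 2[1 − Φ(1.96/√ratio)]. A ratio of 1.47 gives 10.6%, 1.00 gives 5.0%, 0.53 gives 0.7% and 0.47 gives 0.4%. Simulation with 8 schools per arm and 3000 trials per scenario gave 0.5% to 10.5%.

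Two omissions pull in opposite directions. Without school-by-time variance the SE is too small. Without a child-level term, taking the model literally, it is too large.

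**4. If a fuller plan adds a child intercept but no school-by-time term.** The denominator becomes vc(1 − rc) + vs(1 − rs), and the offset disappears.

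- m = 37, rs = 0.8, rc = 0.3: 0.901/0.685 = 1.32
- m = 37, rs = 0.3, rc = 0.7: 1.068/0.312 = 3.42

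The ratio exceeds 1 whenever rs < 1, so the test is then always anti-conservative.

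**5. A change-score model behaves properly.** With child change scores, a school random intercept and the arm effect as the test, the simulated model SE tracked the empirical SD: 0.099 against 0.090 at school correlation 0.8, and 0.118 against 0.120 at 0.5.

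**The case against.** **The article does not say the school intercept is the only random effect.** This is true, and a condensed article may leave the within-child covariance and the degrees-of-freedom method to a fuller plan. Their absence is not counted as an error here. A reader might infer that the test will be referred to thousands of child-level degrees of freedom, but the document does not say so. What stands is that the article assigns the clustering adjustment to an intercept that cannot supply it for the named coefficient. Adding only a child effect would not cure that.

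**The outcomes are described as changes.** If change scores were modelled and the arm effect tested, the school intercept would carry the right variation. The wording is open to that idea, but the text names the interaction as the key coefficient, and the intercept cancels from an interaction with time.

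**If school effects were perfectly stable over time, their cancellation would be correct.** This is also true: with no school-by-time variance, a child-level term alone would suffice. A school-randomised trial should not build that assumption in unstated.

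**Harm is not shown in one direction.** This stands in full. The type I range straddles 5%, and the middle of the assumed grid gives about 5.0% at 37 children per school and 3.6% at 28. It would be tempting to say that the standard error is simply too small, or to quote error rates of 8% to 30%. The documents do not support the first, and those rates belong to the model in step 4 of the working, which the protocol does not state.

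**Conclusion.** The point holds as a defect in what the article states: the named clustering device does not act on the named test, and between-school variation in change is absent from the stated model. The cancellation is algebraic and needs no assumption beyond balance; without balance it is near-complete.

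The consequence is a type I error that the plan does not control. For the model taken literally it lies between about 0.5% and 10.5%, given ICC 0.03, 28 to 37 children per school, 8 schools per arm and the assumed correlations over time. It is near nominal only in special cases or where the two omissions happen to offset. The direction cannot be settled from the documents. If a child-level term is in the unshown plan and a school-by-time term is not, the error is anti-conservative whenever schools differ in their change.

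**What to change.** Amend the analysis paragraph in one of two ways.

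- **Keep the interaction as the test.** Add a school-by-time random effect (or school random slopes) together with a child random effect or a within-child covariance structure. Use degrees of freedom that reflect the number of schools, for example Kenward-Roger.
- **Or test the arm effect directly.** Model child change scores, or the follow-up value adjusted for baseline, with a school random intercept, again with degrees of freedom that reflect the number of schools.

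State that the same structure applies to the cognitive and academic outcomes. The separate comparisons of each program with control can stay; a single three-arm model is optional and not part of this correction.

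The cost is a few sentences and a few lines of SAS, with no change to data collection or sample size. Intervals may widen or narrow, depending on the correlations found.

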## Discussion

The Fueling Learning through Exercise (FLEX) Study will contribute to the evidence base on strategies for increasing children’s engagement in PA at school by using objective measures of physical activity to evaluate the impact of two innovative, low-cost, school-based PA programs on children’s PA as well as on their cognitive functioning and academic success. Demonstration of a relationship between school-based PA with neutral or improved, rather than diminished, academic outcomes has the potential to positively influence school administrators’ investment in PA programs and initiatives.

The participants in the FLEX Study are from racially- and ethnically-diverse, primarily low-income communities. Rising inequalities in the prevalence of childhood obesity [54] and lack of demonstrated success to increase PA in high-risk children further underscore the need to identify PA interventions with equitable reach [55]. PA programs should reach all children as opposed to making the “fit kids fitter” or failing to impact MVPA in those who are overweight or obese. A recent evaluation of MVPA among inner-city elementary schoolchildren based on accelerometry found substantial disparities, such that MVPA was lower among females, Hispanics, and overweight and obese children [35]. Accelerometry studies based on nationally-representative samples such as NHANES indicate an even more complex relationship between PA and gender, weight status, and race/ethnicity [56]. Belcher et al. found that while obese youth were generally less active, this did not hold true across all racial/ethnic groups. These findings, and others, suggest that social and environmental supports may be critical ecologic contributors to reducing disparities observed in MVPA among underserved youth [57, 58].

However, disparities in PA-supporting policies and practices, such as lower-SES schools being less likely to have PE teachers and fewer supporting PE practices compared to higher-SES schools, may further undermine the ability of underserved youth to achieve recommended PA levels [17]. These findings indicate an even greater need for structured recess as well as before- and/or after-school and classroom-based PA opportunities to supplement PE time in these environments, and further suggest that school-based PA programs have the potential to attenuate disparities. Understanding the effects of such programs over time and correlates of participation in them among diverse schoolchildren at high risk of obesity is essential to the design and expansion of effective interventions with the potential to achieve a broad reach and attenuation of health disparities, and support children in developing healthy lifestyle habits.

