**Discussion:**

The FLEX study will evaluate strategies for increasing children’s MVPA through two innovative, low-cost, school-based PA programs as well as their impact on children’s cognitive functioning and academic success. Demonstration of a relationship between school-based MVPA with neutral or improved, rather than diminished, academic outcomes in a naturalistic environment has the potential to positively influence investment in school PA programs and initiatives.

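### The article names a demonstration of neutral academic outcomes as a policy-relevant result, but the only decision rule it gives for them, a difference test at p<0.05, cannot demonstrate neutrality

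*Protocol article*

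**What the plan says.** The claim appears twice in the protocol article. The main Discussion names "Demonstration of a relationship between school-based PA with neutral or improved, rather than diminished, academic outcomes" as something that could favourably affect investment in activity programmes. The Discussion part of the Abstract says the same, referring to "neutral or improved, rather than diminished, academic outcomes in a naturalistic environment".

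The rule is in the section on sample size and data analyses. For MVPA, the programme-by-time coefficient shows "if the intervention is associated with a significant higher/lower change in MVPA across time compared to the control", and the authors will "conclude if the difference in MVPA minutes is statistically significant". For the other outcomes: "A similar approach will be used to examine the impact of PA programming on academic/cognitive outcomes". The closing criterion is that "results with p-values less than 0.05 will be considered statistically significant".

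The section states no largest acceptable decline for academic or cognitive scores and no confidence-interval rule for calling a result neutral. The sample size is justified for MVPA only. The Aims section puts the academic question without direction, as an evaluation of effects.

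**The concern.** A two-sided difference test has two informative outcomes, significantly higher and significantly lower. A third outcome, not significant, is compatible both with no effect and with a decline that the trial was too imprecise to detect. To demonstrate that scores are not diminished, declines beyond some size must be excluded, and p>0.05 does not do that.

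The Background names pressure from standardised tests and a crowded curriculum among the reasons why activity has been limited in schools. Whether activity time costs achievement is therefore a question administrators will bring to the results. If the p<0.05 rule is the only tool, reassurance becomes easier to obtain as precision falls: more clustering, more loss and noisier scores all make non-significance more likely. A sound rule for a no-decline conclusion works the other way.

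**Working it through.** **Step 1. The article's own sample size.** Inputs from the sample size section: "mean ± SD: 53.4 ± 25.6 vs. 43.5 ± 27.6" (percentage of recess time in MVPA), "with power of 80" %, 7 schools per arm, ICC 0.03, 25 % attrition per year.
- Pooled SD = √((25.6² + 27.6²)/2) = 26.6; difference = 53.4 − 43.5 = 9.9; d = 0.372.
- Two-sided 5 %, 80 % power: 114 per arm by the normal approximation, 115 with the t distribution. The article states 115.
- Fixed number of clusters: m = n(1−ICC)/(k − n·ICC) = 115 × 0.97/(7 − 3.45) = 31.4, rounded up to 32; 32/0.75 = 42.7, rounded up to 43; 43 × 21 = 903. The article states 903.

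The figure reproduces, with one 25 % loss. It concerns MVPA and says nothing about the precision of academic scores.

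**Step 2. What the difference test would do with a real academic decline.** From the article: 24 schools in three arms, so 8 per arm if allocation was equal; 174 + 1008 = 1182 pupils, so 1182/24 = 49.25 per school; 36.9 per school after one 25 % loss; ICC 0.03. Assumed, because the article gives no such figures: scores in SD units (SD = 1), a true decline of 0.20 SD, the MVPA ICC applied to scores, and a baseline correlation r of 0, 0.7 or 0.8.

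Formulae: DE = 1 + (m−1)·ICC; SE = √(2·DE·(1−r²)/(8m)); 95 % half-width = 2.145·SE (t, 14 df). The miss rate is the probability that the test is not significantly negative, from the noncentral t with 14 df and noncentrality −0.20/SE.

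| Pupils per school | DE | r | SE | Half-width (SD) | Decline missed |
|---|---|---|---|---|---|
| 49.25 (no loss) | 2.45 | 0 | 0.112 | 0.239 | 61 % |
| 49.25 | 2.45 | 0.7 | 0.080 | 0.171 | 35 % |
| 49.25 | 2.45 | 0.8 | 0.067 | 0.143 | 21 % |
| 36.9 (one 25 % loss) | 2.08 | 0 | 0.119 | 0.254 | 65 % |
| 36.9 | 2.08 | 0.7 | 0.085 | 0.182 | 41 % |
| 36.9 | 2.08 | 0.8 | 0.071 | 0.153 | 26 % |

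**Step 3. Sensitivity.** With 36.9 pupils per school and an assumed ICC of 0.10, DE = 4.59. The miss rate is then about 82 % without adjustment and about 58-68 % with r = 0.8-0.7. With two successive 25 % losses (27.7 per school) and ICC 0.03, it is about 69 % without adjustment.

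**Step 4. How far baseline adjustment can be relied on.** The factor 1−r² is that of an analysis adjusted for baseline: 0.51 at r = 0.7 and 0.36 at r = 0.8. A pure change score has variance factor 2(1−r), which is 0.60 and 0.40, so it gains slightly less. The Academic outcomes section says that state testing covers grades 3-10, and Table 1 takes baseline scores from the preceding spring. Pupils enrolled in grade 3 would normally have been in grade 2 then and may have no prior state score. For Math and ELA the full gain may therefore not be reached. The cognitive tests have a baseline measurement at entry.

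**Step 5. The same precision under a confidence-interval rule.** If the true difference is zero and the largest acceptable decline were 0.20 SD (illustrative only), the chance that the lower 95 % limit clears it is, by symmetry, one minus the miss rate in the table. That is about 35-39 % without adjustment and 59-79 % with it.

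**The case against.** A reader might infer that the trial will report any non-significant academic result as neutral. The documents do not support that: no sentence says how p>0.05 will be interpreted for any outcome. A reader might also infer that academic decline is treated as a harm or safety endpoint, or that a non-inferiority trial was declared. Neither is so. The article speaks only of diminished outcomes, in a sentence about policy relevance, and the non-directional aim fits a two-sided test. Those points stand, and they limit the concern to a mismatch between a stated hope and the stated rule.

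It can also be said that a margin and wording for null results belong in an analysis plan that is not shown. This stands in part, since such a plan may contain them. But the article does more than leave the matter open. It names the conclusion sought, and it fixes a decision rule for these outcomes that cannot deliver it.

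The third objection is about size, and it is right. Miss rates of 65 % (ICC 0.03) or 82 % (assumed ICC 0.10) ignore baseline information, although the plan analyses change from baseline. They also apply a 25 % loss to scores that come from state records and need not be lost when a child misses a school visit. The adjusted figures belong beside the unadjusted ones.

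**Conclusion.** The concern holds as a gap between conclusion and method. The article offers a demonstration of neutral or improved academic outcomes as a useful result, and the p<0.05 rule can support improved or diminished but not neutral. That logic depends on no assumed figure.

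The practical size does. At ICC 0.03, with 8 schools per arm and 37 to 49 pupils per school, a true 0.20 SD decline would go undetected in about 61-65 % of trials without baseline adjustment. With a baseline correlation of 0.7-0.8 this falls to about 21-41 %. The decline, the SD scale, the correlation and the use of the MVPA ICC for scores are assumptions. Even in the most favourable case shown, about one trial in five would miss the decline. The effect estimates themselves and the MVPA comparison are not affected.

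**What to change.** In the data-analysis section, or in the analysis plan if it is still open:

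1. State that p>0.05 will not be interpreted as a neutral effect.
2. For Math, ELA and each cognitive score, report the 95 % confidence interval for each programme minus control, in SD units.
3. Conclude neutral or improved only if the lower limit lies above a largest acceptable decline, fixed and justified before the outcome data are analysed. Otherwise report: *inconclusive; a decline of up to X is not excluded*, with X read from the interval.

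This takes one paragraph and needs no new data, schools or visits. The downside is that a null result may have to be reported as inconclusive. Step 5 of the working shows that this could happen often even if the programmes truly have no academic effect.
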